#### Intervention Targets

In 2013, an obesity expert panel reviewed 146 lifestyle intervention studies and reported a high degree of evidence for the effectiveness of diet with caloric restriction and increased physical activity for weight loss in adults [73]. Behavioral interventions to treat obesity are deemed safe for youth (4-18 years); however, fostering healthy eating behaviors is recommended over caloric restriction for weight loss in youth [74]. Thus, the dietary targets for children are to increase fruit and vegetable consumption, reduce sugar-sweetened beverage intake, and adopt appropriate portion sizes. The dietary targets for parents are to reduce the overall caloric intake by reducing the consumption of sugar-sweetened beverages and dietary fat and to increase fruit and vegetable intake. According to the 2018 Physical Activity Guidelines [75] and the 2009 American College of Sports Medicine Position Statement [76], the family (parent and child) physical activity goal is 60 minutes of moderate-to-vigorous activity (3 or more metabolic equivalents) per day on 5 or more days per week. In addition, based on the recommendations for treating obesity and reducing T2DM risk in youth, the sedentary target will be to reduce out-of-school time watching television, playing video games, and/or using a tablet, iPad, or smartphone to less than 2 hours per day.

#### Intervention Sessions

Group sessions will consist of identifying behavior change strategies leading to achieving the intervention targets (20 minutes), problem solving and decision making to circumvent barriers (20 minutes), and family goal setting and action planning (20 minutes). Parents will be coached to self-select behavior change strategies and practice skills that will enable them to do things such as making healthy foods available in the home, modifying recipes to be healthier, reading food labels, increasing family physical activity, and creating boundaries for the use of technology to reduce out-of-school sedentary time. Parents will be encouraged to use behavioral reinforcement strategies with their children, such as giving immediate praise, creating realistic expectations, and rewarding effort [77]. The practice of brainstorming will be used to encourage parents as a collective group to self-discover solutions to behavior change barriers and support participants in achieving their goals. Brainstorming has proven to be an effective component of problem solving and mitigating barriers to sustainable behavior change [78-82]. Action planning will be used to facilitate parents in setting realistic, attainable, and short-term (weekly) goals for making dietary and physical activity changes. Goal setting positively correlates with weight loss [83], and action planning is an effective self-monitoring strategy that will allow participants to personalize their goals and gradually achieve intervention targets [84,85].

#### Intervention Participant Retention

Telehealth is an effective retention strategy used in the DPP [86] and mitigates transportation barriers [87]. The lifestyle coach will dedicate time outside of intervention sessions to build rapport with parents and will function as a personal contact for participants to establish meaningful relationships, send meeting reminders, and schedule and conduct make-up sessions (consistent with DPP [63]) [86]. Participants will be incentivized using attendance raffles for cooking (eg, measuring cups), physical activity equipment (eg, jump rope), and incremental monetary compensation at each assessment point (baseline, US $50; postintervention, US $75; follow-up, US $150) [86]. Study assessments will be conducted in-person at the time of the child’s routine appointment with the pediatric weight management clinic and monetary resources will be allocated to families experiencing transportation barriers.

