### Intervention

Power to Prevent [28] is a diabetes prevention intervention based on the DPP [63] and the *Small Steps, Big Rewards Program* [69] and is tailored for AA families. The goal of the program is to achieve a 5% to 7% weight loss by making modifications to dietary, physical activity, and sedentary behaviors. In the proposed pilot trial, modification to family dietary, physical activity (≥150 min per week), and sedentary behaviors will be targeted, in addition to individual-level parent behaviors. The *Power to Prevent*
*Leader Guide* and participant materials will be adapted and used in each session. The scientific literature strongly supports family-based approaches to treating youth with overweight or obesity [70]. Thus, group-based sessions (60 min) will be conducted with parents and target the adoption, maintenance, and self-regulation of family-focused dietary, physical activity, and sedentary behaviors. Parent participants will meet weekly for 11 weeks and then monthly for 4 pilot maintenance sessions (15 sessions in total; frequency and duration supported by the literature [71]). Sessions for all groups will be facilitated by a racially concordant lifestyle coach (interventionist) who will be trained in accordance with the Centers for Disease Control and Prevention Diabetes Prevention Recognition Program standards [72]. Wi-Fi–equipped iPads (12.9”) with cellular connectivity will be used to link families to videoconferencing sessions and to cooking and family-friendly physical activity video demonstrations via YouTube.

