	**Home physical and social environment**			
		Modified Home PA and Food Environment Scale, 100 items (Gattshall et al [97]); subscales: availability and accessibility of food, physical activity equipment, and technology devices; parent role modeling and family policies for food, physical activity, and technology use	Parent	

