#### Evaluation Data Sources

Five data sources will be used to gather sufficient evaluation data. Brief qualitative interviews will be conducted with providers (across and within waves) and families (within waves) at 3 time points: (1) during the intervention, (2) at postintervention, and (3) at follow-up. Family interviews during the intervention will be conducted by the PI via phone at the families’ convenience, and postsession and follow-up interviews will be conducted in-person during study assessments at the clinic. Provider interviews will be conducted by the PI via Big Blue Button on the UMMC campus. Interviews will probe providers’ and families’ perceptions of the acceptability, feasibility, and appropriateness of the intervention and the impact of telehealth on patient and provider engagement, provider partnerships, treatment outcomes, and access to care. Providers and the PI will also meet weekly for 30 minutes via Big Blue Button to review protocols, discuss implementation progress, identify barriers and solutions, and create action plans for adaptations to improve recruitment, retention, and intervention delivery.

Parents and the lifestyle coach will be asked to complete brief postsession surveys using their iPads to assess the acceptability and appropriateness of the intervention content, materials, and delivery. The lifestyle coach will be asked to document participation, the *Power to Prevent* resources that were used, and session components that were delivered and be asked to describe what worked well and the obstacles encountered. The lifestyle coach will record formal attendance and outreach encounters to document participant attendance at each core session and maintenance session, make-up sessions, and any outreach encounters via email, phone, or text message. Session observations will be conducted by the PI using an observation guide during one-third of all sessions to assess implementation fidelity, family engagement, and interactions among families and the lifestyle coach (context).

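### Raffled exercise equipment and study iPads overlap with two availability subscales of a secondary outcome, so change on those subscales can partly reflect trial supplies

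*Protocol article*

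**What the plan says.** Four parts of the protocol article bear on this.

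- **Incentive.** Under Intervention Participant Retention: "Participants will be incentivized using attendance raffles for cooking (eg, measuring cups), physical activity equipment (eg, jump rope"), alongside payments at each assessment. The prizes are presented as a retention measure, not as part of the lifestyle programme.
- **Device.** Under Intervention, iPads "with cellular connectivity will be used to link families to videoconferencing sessions" and to cooking and activity videos. Under Evaluation Data Sources, parents are "asked to complete brief postsession surveys using their iPads", so the devices are in their hands while the programme runs.
- **Outcome.** Under Intervention Efficacy Measures, the home food and physical activity environment is a secondary outcome, assessed at weeks 1, 12 and 30. Table 1 gives the instrument as the "Modified Home PA and Food Environment Scale, 100 items", completed by the parent. Its content includes "availability and accessibility of food, physical activity equipment, and technology devices", and also "parent role modeling and family policies for food, physical activity, and technology use".
- **Design and analysis.** The trial has one arm and 20 parents. The first Data Analysis section plans an adjusted comparison of the environmental measures. It does not mention items that the study itself supplied.

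**The concern.** The Conceptual Model section describes helping families change the home food, activity and screen-time environment, and the scale is there to show whether that happened. If the study puts exercise equipment and a tablet into the home between two administrations, a parent who answers the availability items literally may count them. The subscale then records what the study delivered, together with anything the family did for itself.

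In a controlled trial, supplies common to both arms would largely cancel. Here nothing cancels them. The section on sample size also says that the pilot will yield effect sizes for designing a later randomised trial, so a shift caused by supplies could be carried into that trial's planning for this outcome.

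**Working it through.** The plan states no figure on this point, so there is none to reproduce. The check has two parts.

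**1. Supplies set against the content of the scale**

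| Study supply | Who receives it | Matching content in Table 1 |
|---|---|---|
| Physical activity equipment | Raffle winners only | Availability of physical activity equipment |
| iPad | Parents, during the intervention | Availability of technology devices |
| Cooking items | Raffle winners only | None listed |
| None | – | Food availability, role modelling, family policies |

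Two kinds of content are exposed and the rest is not. Four facts that would fix the size are not given: how many families win equipment, whether the iPad is lent or given, whether it is issued before or after the week 1 assessment, and whether the items count pieces or record presence.

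**2. How large the shift could be (illustration)**

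Inputs from the article: two-sided alpha 0.05; n = 20 with no attrition, and 20 × 0.80 = 16 at 20% attrition.

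Assumptions, not in the article: a share p of families gains exactly one counted item because of the study; all other change has mean 0 and SD s items; the analysis is a one-sample t test of change.

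Mean change = p. Variance of change = p(1 − p) + s². Standardised shift d = p / √[p(1 − p) + s²]. The chance of a significant increase is the upper tail of a noncentral t with n − 1 degrees of freedom and noncentrality d√n, beyond the two-sided 5% critical value.

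- Example, p = 1 and s = 1: d = 1/√(0 + 1) = 1.00, giving 0.96 at n = 16 and 0.99 at n = 20.
- Example, p = 0.25 and s = 1: d = 0.25/√(0.1875 + 1) = 0.23, giving 0.14 and 0.16.

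Chance of a significant increase from supplies alone, n = 16 to n = 20:

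| Share gaining one item | s = 0.5 | s = 1 | s = 2 | s = 5 |
|---|---|---|---|---|
| 25% | 0.29–0.36 | 0.14–0.16 | about 0.07 | about 0.04 |
| 50% | 0.75–0.85 | 0.39–0.48 | 0.15–0.18 | about 0.06 |
| 100% | about 1.00 | 0.96–0.99 | 0.46–0.56 | 0.11–0.13 |

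With no supplies the value would be 0.05/2 = 0.025. The 100% row corresponds to an iPad that every family receives after baseline and every parent counts. The lower shares are closer to a raffle. A small s suits a short availability subscale with little other change, and a large s is closer to a total over 100 items. The effect can therefore dominate a short subscale and be negligible in the total.

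**The case against.** The strongest reply is about the construct. A raffled jump rope really is equipment available in the home, and a single-arm study of a delivered package may fairly count everything the package brought. This stands as a reason not to discard the supplied items. It does not remove the need to know how much of the change they explain, and reporting both ways answers it.

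A second reply is that respondent instructions and prize logs belong in the full protocol or the study forms, and that the wording of the modified scale is not shown. That is fair for the missing instruction taken alone. The point rests instead on two choices that the article does state: what is handed out and what is scored.

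Several stronger readings are tempting, and the document does not support them.

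- **That the whole home-environment score must move.** Only two kinds of content are exposed, and equipment goes to winners only.
- **That cooking prizes add to the effect.** They match no listed subscale.
- **That the direction is fixed.** Scoring is not shown. If items record presence, a family that already owns such an item does not change. More devices might also score unfavourably, so the two shifts could offset each other in a total.
- **That study sessions inflate screen time.** The limit ("using a tablet, iPad, or smartphone to less than 2 hours per day") is an intervention target, not a scored outcome. It rests on recommendations for youth, while the sessions are for parents. The objective sedentary outcome comes from an accelerometer.
- **That attendance raffles create a false link between attendance and home environment.** The Data Analysis section for the efficacy outcomes plans no such analysis. The implementation section mentions only a general side-by-side synthesis with efficacy outcomes.

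**Conclusion.** The point holds in a narrow form. Study supplies overlap with the equipment and device availability subscales of one secondary outcome, and without a control arm a before-after change on these two subscales cannot be attributed wholly to family behaviour.

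The size cannot be derived from the article. The illustration runs from almost no effect to near-certain significance, depending on an assumed share of families and an assumed SD. The iPad part further assumes that the device arrives after the week 1 form, is still in the home at the later assessment, and is counted by the parent. If it is issued before baseline, it need produce no change from baseline to week 12.

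The food, role-modelling and policy content, the child BMI z score and the parent BMI are untouched. This is a minor improvement to interpretability and does not threaten the trial's main conclusions.

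**What to change.** 1. Log raffle prizes and study iPads by family, with the dates of issue and return.
2. At weeks 12 and 30, add one line to the equipment and device items asking the parent to mark anything supplied by the study.
3. Report these two subscales with and without the study-supplied items.

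Alternatively, raffle only items that the scale does not score. That removes the equipment part but leaves the iPad part.

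The cost is one added line in the REDCap form, a short log and one extra sensitivity analysis. No visits or staff are added, and the rest of the scale and the primary outcomes need no change.

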#### Intervention Efficacy Measures

Primary and secondary outcome measures will be assessed at baseline (week 1), postintervention (week 12), and 4-month follow-up (week 30). The primary outcome measure will be a reduction or stabilization in the child BMI *z* score (index participant) and a reduction in parent BMI (coparticipant) [88]. Secondary outcomes include anthropometric (waist circumference and body composition), biomarker (HbA_1c_, blood pressure, resting heart rate, lipid profile, and Tanner stage), behavioral (fruit and vegetable, sugar-sweetened beverage, and sweat and salty snack consumption; family meal frequency; fast food meal frequency; physical activity volume; and sedentary time), psychosocial (self-efficacy, self-regulation, readiness to change, family functioning, and perceived stress), and environmental (home food and physical activity environment and perceived neighborhood support for healthy eating and physical activity) measures (Table 1). All the measurements will be recorded electronically using REDCap (Research Electronic Data Capture) tools hosted at the UMMC [89]. REDCap is a secure, web-based software platform designed to support data capture for research studies, providing an intuitive interface for validated data capture; audit trails for tracking data manipulation and export procedures; automated export procedures for seamless data downloads to common statistical packages; and procedures for data integration and interoperability with external sources.

**Table 1 table1:** Pilot trial outcome measures.

Outcome measure and instrument				Participant
**Anthropometric measures**				
	**BMI *z* score**			
		Stature (0.1 cm) assessed using Seca stadiometer, and weight (0.1 kg) assessed using Tanita (TBF-400) body composition and weight scale; height and weight measured without shoes; BMI *z* score using a CDC^a^ SAS program for the 2000 growth charts ages 0 to <20 years [90]	Child	
	**BMI**			
		Stature (0.1 cm) assessed using Seca stadiometer, and weight (0.1 kg) assessed using Tanita (TBF-400) body composition and weight scale; height and weight measured without shoes; BMI calculated using the CDC formula: weight (kg)/(height [m])^2^ [91]	Parent	
	**Body composition**			
		Tanita (TBF-400 Body Composition Monitor) uses bioelectrical impedance to assess fat and fat-free mass	Parent and child	
	**Waist circumference**			
		Seca 203 ergonomic circumference measuring tape	Parent and child	

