**Methods:**

This single-arm trial will enroll 20 parents with overweight or obesity of children (8-11 years) with overweight or obesity, both of whom are at risk for T2DM. Parents will meet in small groups (5 parents per group) weekly for 11 weeks and then monthly for 4 monthly maintenance sessions via videoconference using Wi-Fi–enabled iPads with cellular connectivity. The intervention will be adapted from the National Diabetes Prevention Program and *Power to Prevent*, a diabetes prevention program tailored for AA families. The same lifestyle intervention facilitated by a racially concordant lifestyle coach trained in the Diabetes Prevention Program will be delivered to all groups (n=4). Participants will be recruited in-person during patient encounters at the UMMC’s pediatric weight management clinic. Sessions will consist of dietary and physical activity behavior change strategies facilitated using problem-solving and goal-setting skills. The implementation strategy has 2 targets: the pediatric weight management clinic site and clinical team and parents of children at risk for T2DM engaged in intensive obesity treatment to prevent T2DM. The multifaceted implementation protocol includes 4 discrete strategies: creating a new clinical team, changing the service site, intervening with families, and promoting organizational readiness for change.

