### Participant Recruitment and Sample Size

In-person participant screening and enrollment will be conducted in the UMMC pediatric weight management clinic beginning in December 2020. Preliminary screening will the conducted by the clinical provider using a patient eligibility checklist that will screen for both child and parent eligibility. The lifestyle coach will immediately meet in the clinic room following the clinical encounter to conduct a full screening and provide detailed study information to interested parents and children. Consent forms will be verbally described to parents and children, and parent consent, parent permission, and child assent will be obtained before study enrollment.

Children will be eligible to participate if they are AA, overweight or obese (≥85th percentile for age- and sex-specific BMI), and aged between 8 and 11 years. The child age range was selected to allow for intervention occurring before the average age of youth-onset T2DM, 13 years [10]. The criteria for parents (biological, grandparent, or legal guardian) of eligible children included AA, overweight or obese (BMI ≥25 kg/m^2^), and coresidence with the child. Although mothers represent most participants in family-based studies, we will not use parents’ sex as an inclusion criterion. Parents and children must also be at risk for T2DM based on the following criteria: (1) parents’ T2DM risk will be assessed using the A1CNow^+^ system to measure point-of-care hemoglobin A_1c_ (HbA_1c_), which uses a drop of nonfasting blood (5.7%-6.4%), and the ADA prediabetes screening tool (score ≥5); (2) child risk will be based on the BMI percentile (≥85th percentile) and parents’ risk (BMI ≥25 and ADA screening or HbA_1c_).

Consistent with previous T2DM prevention interventions [26,57], we will exclude families if the child or parent has a history of T2DM or a screening HbA_1c_ level greater than 6.4%, is taking glucose-lowering medications, is participating in a supervised weight loss program, is pregnant or breastfeeding, has conditions limiting participation, has undergone weight loss surgery, or is moving out of state within 6 months. If a parent becomes pregnant during the study, we will include only child data (index participant) in the analyses. Technology literacy will not be included as an exclusion criterion. Participants will receive technology instruction from the telehealth center and be provided technical support as needed.

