### Data Analysis

Participant sociodemographic characteristics at baseline will be described using means and SDs, medians and ranges, or frequencies with percentages where applicable. The primary outcome evaluation will assess the change in child BMI *z* score (index participant) and parent BMI (coparticipant) from baseline to 12 and 30 weeks using repeated measures analysis of covariance with child Tanner stage as the covariate. Secondary analyses will include the comparison of anthropometric, biomarker, behavioral, psychosocial, and environmental measures adjusted for other factors. Generalized linear modeling will be used to assess the effect of the intervention, both unadjusted and adjusted (controlling for demographics, baseline BMI *z* score, and BMI). Data will be analyzed according to intention-to-treat principles [106-108].

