## Results

Recruitment and enrollment began in December 2020, and the first cohort of families will begin the intervention in March 2021. As of March 15, 2021, 10 children and their parents were enrolled in the study; however, intervention delivery had not begun. Future outcomes will be published in peer-reviewed health-related research journals and presented at national, regional, or state professional meetings and conferences. Preliminary findings will position the investigative team to design a subsequent hybrid study that will include a powered pilot randomized controlled trial with a larger sample of families and providers, a usual care control arm, and long-term follow-up; a robust evaluation of a refined implementation protocol; and cost-benefit and return-on-investment analyses.

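### Child waist circumference and fat and fat-free mass carry no height index or age/sex standard, so in a single arm their change from baseline mixes normal growth with the intervention effect

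*Protocol article*

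**What the plan says.** The abstract's Methods paragraph fixes the design: "This single-arm trial will enroll 20 parents with overweight or obesity of children (8-11 years) with overweight or obesity". There is no concurrent comparison. The Results section reserves "a usual care control arm, and long-term follow-up" for a subsequent study. Under Participant Recruitment and Sample Size, children qualify if they are "overweight or obese (≥85th percentile for age- and sex-specific BMI), and aged between 8 and 11 years". Intervention Efficacy Measures sets assessments at weeks 1, 12 and 30 and lists waist circumference and body composition as secondary anthropometric outcomes.

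Table 1 gives BMI separate rows by participant: a z score from the CDC 2000 growth charts for the child, and weight over height squared for the parent. The next two measures have one row each, shared by parent and child. Body composition is a device that "uses bioelectrical impedance to assess fat and fat-free mass". Waist circumference is a "Seca 203 ergonomic circumference measuring tape". Neither row gives a height index, percent fat, percentile or z score.

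The Data Analysis section that follows Table 1 names child Tanner stage as covariate for the primary outcome. For the rest it says: "Secondary analyses will include the comparison of anthropometric, biomarker, behavioral, psychosocial, and environmental measures adjusted for other factors". The generalized linear model is to be fitted unadjusted, and adjusted for demographics, baseline BMI z score and BMI.

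**The concern.** With no control arm, the estimated effect is the mean change from baseline. Any marker that scales with body size then carries two components, the intervention effect and normal growth, and the data cannot separate them. The article deals with this for child BMI and does not carry it to the neighbouring body-size markers.

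The named adjustment does not help. Baseline BMI z score, baseline BMI and demographics explain differences between children. A growth trend shared by all children is part of the mean change itself and stays in the estimate.

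Two things are at stake. Child waist and fat mass, which ought to support the primary child result, could appear unchanged or worse beside a favourable BMI z score. And the sample-size section says that the pilot will supply effect sizes for a later randomised trial. A pre-post effect that includes growth is a poor input for a controlled comparison, in which growth would cancel between arms.

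**Working it through.** **The only nearby figures in the article.** Evaluable dyads at 10% and 20% attrition: 20 × 0.90 = 18 and 20 × 0.80 = 16. Both reproduce. The article gives no growth rate, SD or power for child waist or fat mass, so every growth and SD value below is an assumption.

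**Waist drift with no change in relative adiposity.** Assume height gain of 5 to 6 cm per year and a constant waist-to-height ratio of 0.55 to 0.65.

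- Week 1 to 30: 29/52.2 = 0.556 year. Height gain is 0.556 × 5 = 2.8 cm to 0.556 × 6 = 3.3 cm. Waist gain is 2.8 × 0.55 = 1.5 cm to 3.3 × 0.65 = 2.2 cm (unrounded 1.53 to 2.17).
- Week 1 to 12: 11/52.2 = 0.211 year. Height gain is 1.05 to 1.26 cm, and waist gain 0.6 to 0.8 cm.

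**Relative to sampling error.** Assume an SD of waist change of 4 cm.

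- n = 18: SE = 4/√18 = 0.94 cm. The week-30 drift is 1.6 to 2.3 SE and the week-12 drift 0.6 to 0.9 SE.
- n = 16 (the attrition that the article anticipates): SE = 4/√16 = 1.00 cm. The drifts are 1.5 to 2.2 SE and 0.6 to 0.8 SE.

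**Fat and fat-free mass.** Assume 20 kg fat, 30 kg fat-free mass, height 140 cm rising to 143 cm, and unchanged mass/height² indices. (143/140)² = 1.043, so fat mass rises by 20 × 0.043 ≈ 0.9 kg and fat-free mass by 30 × 0.043 ≈ 1.3 kg. The first looks unfavourable and the second favourable. Neither reflects the intervention.

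**How often this would mislead.** As a simple stand-in for the planned model, take a paired two-sided t-test on unindexed waist at α = 0.05 with n = 16. Drift = annual waist growth × 29/52. The noncentrality parameter is (drift − benefit)/(SD/√16) on 15 degrees of freedom. Waist growth is varied from 1 to 4 cm per year, which contains the 5 × 0.55 = 2.75 to 6 × 0.65 = 3.9 cm per year implied above. Ranges within cells are over SD 2 to 4 cm.

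| Waist growth, cm/year | Drift, cm | P(significant increase), no effect | Expected change with a true 1 cm benefit, cm | P(significant decrease), 1 cm benefit |
|---|---|---|---|---|
| 1 | 0.56 | 0.08 to 0.18 | −0.44 | 0.06 to 0.13 |
| 2 | 1.12 | 0.18 to 0.55 | +0.12 | 0.015 to 0.019 |
| 3 | 1.67 | 0.35 to 0.88 | +0.67 | 0.001 to 0.005 |
| 4 | 2.23 | 0.55 to 0.99 | +1.23 | at most 0.001 |

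The nominal rate for the third column is 0.025. With growth removed, the chance of a significant decrease for a 1 cm benefit is 0.15 to 0.46. Growth of 1/(29/52) ≈ 1.8 cm per year cancels a 1 cm benefit exactly.

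**The case against.** The strongest reply is that Table 1 is a list of outcomes and instruments. It names a tape and a device and states no analysis scale for these rows. Conversion to a ratio, percent fat or z score could be set in a fuller protocol or an analysis plan that is not shown. The unspecified other factors in the secondary analyses could also include height or Tanner stage as time-varying covariates, which could absorb some of the growth.

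Part of this stands. A reader might infer that the article commits to analysing raw centimetres and kilograms. It does not say so; that is a reading of the quantities named. But Table 1 is where the article fixes the form of child BMI, down to the program used, and for body composition it names two masses. Following the outcomes as named would mix growth with effect, and no time-varying growth term is among the covariates that it lists.

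A reader might also infer that growth will make all three measures look worse. The documents do not support that. A rise in fat-free mass is not a worsening. For waist and fat mass the direction is a tendency: with growth of 1 cm per year, SD 4 cm and n = 16, a false significant increase has a probability of only about 0.08.

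It is also fair to say that these are secondary outcomes in a 20-dyad pilot, and that an index could still be derived afterwards from the collected data. That limits the weight of the point. It does not remove the case for fixing the child outcome form before results are seen.

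**Conclusion.** The point holds in a limited form. In this single-arm design, change from baseline in unindexed child waist and fat mass includes normal growth, which tends to mask a benefit. The same growth can mimic a gain in fat-free mass. The covariates named in the article do not remove it.

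On the height-gain and waist-to-height assumptions above, the waist shift is about 1.5 to 2.2 cm by week 30 and 0.6 to 0.8 cm by week 12. Against an assumed SD of 4 cm, the week-30 shift is roughly one and a half to just over two standard errors. None of these inputs comes from the article, and slow growth or a large SD would make the bias small.

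A reader might go further and doubt the child efficacy result itself. That is not supported: the primary child outcome is BMI z score, already standardised for age and sex, and it is not affected.

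**What to change.** In Table 1 and the Data Analysis section that follows it, give the child outcomes their own form, as is already done for BMI:

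- waist: waist-to-height ratio, or an age- and sex-standardised waist z score;
- fat: percent body fat, or fat mass index (fat mass/height²);
- fat-free mass: indexed to height, or reported descriptively;
- raw waist and raw masses: descriptive only.

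Leave the parent measures unchanged. Height is already measured for BMI z score at each assessment, so the cost is wording and no new data collection. One downside should be stated: a height index removes most, but not necessarily all, of the age-related change, so some caution is still needed when reading a pre-post difference.
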